### Trial design

The study is a single masked, two-arm RCT with an embedded qualitative process evaluation. Families will be randomised to the intervention or ETAU arms in a 1:1 allocation ratio. Outcomes will be assessed at baseline prior to randomisation (T0), at midline after the completion of core sessions (T1), at endline after the completion of advanced modules (T2, primary time point) and at follow-up 6 months after endline (T3).

The trial employs a sequential, dual outcomes approach to establish effectiveness through multiple pathways comparing treatment *versus* control conditions: (1) upstream improvements in family functioning, parenting practices or caregiver mental health in the full sample; (2) direct improvements in mental health in high-distress adolescents; or (3) enhanced protective effects of upstream improvements on adolescent mental health. Secondary exploratory analyses will examine mechanisms of change over time and the additive effect of the optional modules compared to core modules.

The embedded process evaluation will evaluate implementation, effectiveness and potential sustainability of core and optional modules through mixed methods, including surveys, programme monitoring, staff debrief meetings and qualitative interviews and focus groups. Qualitative activities will be conducted post-intervention (T2) with families who complete and drop out of the intervention, facilitators, outreach staff and other key personnel.

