### Intervention and control conditions

#### Whole-family intervention: StrongerTogether

Intervention characteristics are reported in accordance with the template for intervention description and replication (TIDieR) checklist (Hoffmann et al., 2014). StrongerTogether is a modular, whole-family intervention addressing multiple interconnected family challenges simultaneously. It is positioned as a Level 3 intervention on the IASC MHPSS pyramid,^1^ providing focused, non-specialised mental health support for individual families with psychological distress (IASC, 2007). Non-specialised services rely on task-sharing, an evidence-based approach involving the delivery of mental health services by trained providers who do not have specialised or formal mental health training, improving accessibility (Kazdin, 2019; Raviola et al., 2019).

For each family, the intervention is delivered to at least one caregiver and all adolescents aged between 10 and 17 years. It comprises seven core sessions (including six content-specific sessions and a collaborative ‘transition’ session) addressing family roles, communication, problem-solving and future planning, followed by four optional modules of up to four sessions each covering parenting, caregiver mental health, disagreements and financial literacy, as needed. Session content is manualized, a detailed overview of which can be found in Table 1. Sessions take place weekly at a community centre and are delivered by one non-specialist facilitator face-to-face with individual families, with the support of an assistant to coordinate logistics and provide activities for younger children who may attend but not engage in the entire session. Each session involves a 90-min guided activity or discussion with the entire family, followed by a 30-min discussion with caregivers alone to consolidate the information and support them in their role to implement the strategies. To facilitate home practice and sharing of content with non-attending family members, session content is summarised and provided to families through simple, illustrated handouts and audio-recordings created by the StrongerTogether master trainer to accommodate varying literacy levels.

**Table 1. tab1:** Module content and aims

Central family intervention module		Number of sessions
Module	Aims	

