1 Our family story	Family develops joint understanding of challenges, goals and strengths of the family Family develops joint understanding of roles and responsibilities Caregivers are encouraged to work together as a team	7
2 How our family wants to be	Family develops a joint understanding of challenges, goals, and strengths of the family Family understands each other and build empathy	
3 Managing difficult feelings and helping each other	Family members build awareness of feelings experienced by themselves and others Family builds skills in grounding and stepping back from thoughts to help them manage difficult thoughts and feelings Family learns how to practice good self-care for positive well-being	
4 Communicating well to support each other	Family understands their common barriers to positive communication Family builds skills in positive communication, including good listening, and expressing themselves	
5 Managing our problems together	Family identifies common problems they are facing Family learns and applies the Stop Think Go problem management steps to their problems	
6 Managing problems when we do not all agree	Family discusses strengths, roles and responsibilities in the family Family identifies common sources of conflict Family learns and applies the Stop Think Go problem-solving steps to problems involving disagreements between family members	
7 Reviewing where we started and where we want to go in the future	Family reviews content learned in sessions Family reviews home practice of strategies and troubleshoots any challenges they have faced Family makes a plan for the future, maintaining progress made through these sessions Facilitator collaboratively determines with caregivers whether they will complete additional modules	

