Reach	Representativeness of the participants who enrol and the individuals’ willingness to participate in the study	Qualitative: Reasons for non-participation or discontinuation Monitoring: Attendance records	Debrief meetings: Barriers to recruitment Quantitative: ReachNow evaluation
Effectiveness	Impact of the intervention on target outcomes, including potential negative effects, heterogeneity of effects and mechanisms of change	Quantitative: Intervention effectiveness; Subgroup analyses; Moderation and exploratory mediation analyses Qualitative: Perceived impact and pathways of change	Monitoring and debrief meetings: Adverse events monitoring Qualitative: Perceived impact and pathways of change
Adoption	Organisational support to deliver the intervention, including acceptance of the intervention among implementing organisations and reasons for (non-)adoption	Quantitative: Moderation of intervention effects by facilitator characteristics	Quantitative: Facilitator competency (FamilyACT) Qualitative: Perceived feasibility, acceptability and sustainability of the intervention
Implementation	Completion of intervention components as intended, as well as acceptability (participants’ use of the intervention) and potential for scale-up	Qualitative: Acceptability of core and optional modules	Monitoring: Completion of modules Qualitative: Barriers and facilitators to implementation; Recommendations for sustainment and scale
Maintenance	The extent to which a behaviour is sustained and the intervention becomes institutionalised	Not applicable to this study	

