### Statistical analysis

#### Effectiveness analyses

Trial results will be reported following the updated recommendations of the Consolidated Standards of Reporting Trials (CONSORT) 2017 statement for randomised trials of nonpharmacologic treatments (Boutron et al., 2017). All analyses will use an intent-to-treat approach, including all randomised participants regardless of intervention adherence. Statistical significance will be evaluated with a significance level of *p* < 0.05 for each step, with analyses proceeding regardless of preceding step results to fully understand intervention mechanisms.

*Primary effectiveness analyses* will test dual outcome hypotheses sequentially to examine intervention effects on upstream and downstream outcomes using hierarchical linear modelling to account for the nested data structure: (1) repeated measurements within individuals; (2) multiple individuals nested within families; and (3) families randomised to intervention or control conditions. T2 is the primary time point for evaluating intervention effects using group × time interactions, accounting for individual-level fixed effects (*e.g.*, age, gender and baseline measures) and random effects at the individual and family levels (*e.g.*, variation in stress over time).

*Secondary exploratory analyses* will test moderation effects and employ latent growth curve modelling to investigate treatment response patterns and mechanisms of change. Sub-group analyses will examine differential effects by facilitator characteristics, module completion and family and individual characteristics, including time since displacement. Sensitivity analyses will include per-protocol analyses limited to participants completing sufficient dosage of core sessions and alternative missing data approaches.

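### Module completion and optional-module uptake arise after randomisation with no control counterpart, so they cannot define effect subgroups, and the per-protocol set is a selected comparison

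*Protocol article*

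**What the plan says.** The Effectiveness analyses section opens with a general rule: "All analyses will use an intent-to-treat approach, including all randomised participants regardless of intervention adherence". Two later sentences in that section use adherence. One concerns subgroups: "Sub-group analyses will examine differential effects by facilitator characteristics, module completion and family and individual characteristics". The other concerns the per-protocol set: "Sensitivity analyses will include per-protocol analyses limited to participants completing sufficient dosage of core sessions".

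The Trial design section adds that "Secondary exploratory analyses will examine mechanisms of change over time and the additive effect of the optional modules compared to core modules". Table 4, in the Adoption row, lists "Moderation of intervention effects by facilitator characteristics". The Sample size section names uptake of the advanced modules among the sub-analyses that support recruiting 550–600 families.

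Three statements fix how these variables come about:

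- The intervention section describes seven core sessions, "followed by four optional modules of up to four sessions each covering parenting, caregiver mental health, disagreements and financial literacy, as needed".
- Table 1 places the decision on further modules in core session 7: "Facilitator collaboratively determines with caregivers whether they will complete additional modules".
- The ETAU section describes one session of 30–45 minutes. It is given by facilitators who are not the StrongerTogether facilitators and who have a separate 1-day training, against 10 days for StrongerTogether.

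**The concern.** A subgroup analysis of a treatment effect compares the arms within levels of a variable that both arms have and that treatment cannot change. Module completion and optional-module uptake meet neither condition. They follow randomisation, they depend on the family's engagement and need and on how the core sessions went, and ETAU families have no value for them.

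The per-protocol set has a related weakness. ETAU families have no core sessions to complete, so the rule can remove families from one arm only, and the comparison loses the protection of randomisation.

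What is at stake is the reading of dose and of the optional modules. The article's background says that evidence on the optional components is now needed from a fully powered trial. It describes the earlier fully powered trial as testing the core sessions only. Read as treatment effects, these analyses could suggest a benefit of dose or of added modules that is only selection, or could hide a real one.

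**Working it through.** **1. Is there a matching control stratum?**

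| Variable | When it is fixed | ETAU counterpart |
|---|---|---|
| Core-session completion | after randomisation | none (single session) |
| Optional-module uptake | core session 7 | none |
| Facilitator characteristics | not behaviour of the family | facilitators exist, but different people with different training |
| T0 family and individual characteristics | before randomisation | yes |

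Only the last row supports a treatment-by-subgroup interaction protected by randomisation. For the first two rows the interaction cannot be estimated, because the variable has no values in the control arm. For facilitators there is no matched contrast, and the article does not describe how families are assigned to them.

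**2. The plan's own figure on uptake.** The Sample size section requires 440 analysable and expects 20% attrition: 440 / (1 − 0.20) = 550. This reproduces the lower recruitment bound exactly, so at 550 nothing is left for uptake sub-analyses. At 600, 600 × 0.80 = 480, which is 40 more than 440.

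**3. Per-protocol bias when the true effect is zero.** Let c be the share who complete. Let g be the gap in expected outcome, in SD units, between completers and non-completers. Randomisation makes the control mean equal to the overall mean, which is the completer mean minus (1 − c) × g. Hence

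bias (completers versus all ETAU) = (1 − c) × g.

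The documents give neither c nor g. Both are assumed:

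- c = 0.8, g = 0.2: 0.2 × 0.2 = 0.04
- c = 0.7, g = 0.3: 0.3 × 0.3 = 0.09
- c = 0.6, g = 0.4: 0.4 × 0.4 = 0.16
- g = 0: 0 at any c
- g negative: same size, opposite sign

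**4. Second route.** Suppose completion follows a normal propensity that correlates r with the outcome. The bias is then r × φ(z_c) / c, where φ is the normal density and z_c the normal quantile of c. Again r and c are assumed:

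| c | r = 0 | r = 0.2 | r = 0.3 |
|---|---|---|---|
| 0.5 | 0 | 0.16 | 0.24 |
| 0.7 | 0 | 0.10 | 0.15 |
| 0.8 | 0 | 0.07 | 0.11 |
| 0.9 | 0 | 0.04 | 0.06 |

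The two routes agree. At c = 0.7 and r = 0.2 the implied gap is 0.331, and 0.3 × 0.331 = 0.099. Completers compared with non-completers inside the intervention arm would differ by 0.32–0.39 SD at r = 0.2 (c from 0.5 to 0.9) with no effect at all.

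**5. Simulation with a true effect of 0.15** (400,000 families per setting). Intention-to-treat returned 0.14–0.15. Completers against all controls returned 0.25 (r = 0.2, c = 0.7), 0.30 (r = 0.3, c = 0.7) and 0.30 (r = 0.2, c = 0.5). When the effect was made to act only through completion, the complier-average estimate (intention-to-treat difference divided by c) returned 0.14–0.15. That shows it works when its key assumption is true; it does not show that the assumption is true here.

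**The case against.** The strongest reply is about status. The optional-module comparison is labelled secondary and exploratory, the per-protocol analysis is labelled a sensitivity analysis, and facilitator moderation sits under Adoption in the process evaluation. This stands: the primary T2 comparison does not depend on any of them.

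A reader might infer four stronger points that the documents do not support:

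- **That every one of these variables exists only in the intervention arm.** ETAU sessions also have facilitators, and their background is not family behaviour after randomisation. What remains is the lack of a matched contrast.
- **That the per-protocol estimate must be biased upwards.** The bias is zero if completion is unrelated to prognosis. Families in greater need may stay longer, which could reverse the sign, and the planned adjustment for age, gender and baseline measures could shrink it. The bias passes 0.15 only in the corner c = 0.6, g = 0.4 of the assumed range in step 3.
- **That takers of optional modules will be compared with non-takers.** The Trial design section does not say so. T1 falls at the boundary between core and optional modules, and the model has group × time terms, so a between-arm contrast of that phase is already available.
- **That the per-protocol analysis is improper.** It is a conventional sensitivity analysis. Replacing it outright would be a preference.

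It can also be said that estimators belong in an analysis plan that is not shown. That is fair for the per-protocol comparator, which the article does not spell out. It does not rescue module completion as a subgroup, because no later detail can make it a baseline variable or give it a value in ETAU.

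**Conclusion.** The point holds in a limited form. Module completion and optional-module uptake cannot serve as subgroups for treatment effects; this follows from the design as described and needs no assumption. The per-protocol analysis compares a selected part of one arm with the other arm, on the natural reading that all ETAU families stay in, and is biased whenever completion is related to prognosis. Direction and size are unknown. The range of 0.04–0.16 SD rests on assumed completion of 60–80% and an assumed gap of 0.2–0.4 SD in favour of completers. That is enough to matter beside a planned effect of 0.15, but it is an illustration and not an estimate for this trial. The primary T2 intention-to-treat result stands, and the T0 family and individual subgroups named in the same sentence are valid.

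**What to change.** 1. Limit subgroup interactions to family and individual characteristics measured at T0.
2. Report module completion and StrongerTogether facilitator characteristics as within-arm, non-randomised associations, here and in the Adoption row of Table 4.
3. Keep the per-protocol analysis as a sensitivity analysis, say that it departs from the general intention-to-treat rule, and add a complier-average causal effect with randomisation as the instrument. State its assumption. A threshold version assumes no effect below the threshold, which is doubtful for families who attended some of the seven sessions. A session-count version assumes a linear dose effect.
4. Answer the question about "the additive effect of the optional modules compared to core modules" from the between-arm difference in T1-to-T2 change. Say that this contrast is randomised but does not isolate the optional modules: it also carries continuing effects of the core sessions and includes families who take no optional module.

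The cost is wording in the article or analysis plan, with no change to the data collected. Complier-average intervals will be wider than per-protocol intervals, and their assumptions must be defended.

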#### Process evaluation

Informed by the Medical Research Council framework for evaluating complex interventions (Skivington et al., 2021), the mixed-methods process evaluation uses the Reach, Efficacy, Adoption, Implementation and Maintenance framework (Glasgow et al., 2019) to assess implementation, effectiveness and potential sustainability (Table 3). Quantitative process data will include records on module attendance and completion, as well as facilitator competency measured using the EQUIP-based FamilyACT tool (all facilitators are observed and rated by a trained competency rater at post-training and after completion of the seven core sessions). Supervisors will directly observe two sessions and complete observational ratings assessing fidelity to the intervention manual and quality of delivery. Regular debrief meetings will be held throughout implementation to document challenges. Debrief notes and qualitative data from semi-structured interviews and focus group discussions with families, facilitators and other stakeholders will be analysed using thematic content analysis (Braun and Clarke, 2025). Process and effectiveness data will be triangulated to better understand which families are most likely to drop out or benefit from the intervention and to explore mechanisms of change.

### Trial and adverse events monitoring

A trial management committee will monitor the implementation of study procedures and protocol deviations. All research staff will follow War Child’s Child Safeguarding Policies and will record any suspected maltreatment, exploitation or other violations and report these cases and other adverse events within 24 hours for review and appropriate action. To manage participant distress, multiple mitigation measures will be in place: (1) research assistants will be trained to recognise signs of distress and remind participants they can skip questions or withdraw at any time during all assessments; (2) referral pathways have been established for families requiring support beyond the scope of the intervention, including those who experience distress during intervention sessions or where severe mental health or protection concerns become apparent; (3) all staff have been trained to refer cases in accordance with safeguarding policies. A Data Safety Management Committee will also be established and mandated to provide oversight on adverse events and safety protocols for the trial.

### Ethics

Ethics approval was obtained from the University of Jordan (ref: 557 / 2025). The core research team also comprises representatives from academic institutions and implementing partners who work closely with the target communities. The team will provide input on study materials, implementation approaches and interpretation of findings to ensure cultural appropriateness and relevance.

Particular attention will be given to the ethical considerations of working with vulnerable populations, including refugees and displaced families. The research team will ensure that participation is voluntary, informed consent procedures are clear and accessible and participants understand their right to withdraw at any time without consequences for their access to services. Families will not receive compensation for their participation in the study; they will only be compensated for transportation costs. Data protection measures will safeguard participant confidentiality, and referral pathways will be established for cases requiring additional support.

### Trial status

Recruitment of study participants will begin in December 2025.

## Discussion

This study aims to demonstrate the impact of an integrated approach to family mental health support for displaced and vulnerable families. It tests both upstream family mechanisms and direct impacts on adolescent mental health, providing evidence for family-systemic intervention pathways. The results will contribute to the evidence base on whole-family mental health interventions in humanitarian settings, an area currently characterised by substantial gaps, despite promising findings from caregiver-focused programmes (Giusto et al., 2025). Such integrated approaches could promote sustainability and scale in humanitarian and low-resource settings (Troup et al., 2021).

Study strengths include rigorous evidence on interventions addressing social determinants of mental health through inclusion of both displaced and host populations, use of non-specialist facilitators following task-sharing approaches (Raviola et al., 2019; Cohen and Yaeger, 2021) and modular design tailoring to family-specific needs (Kazdin, 2019).

Limitations include the complexity of measuring change in multiple outcomes over time through the sequential dual outcomes approach. While our sample size provides adequate power for testing H1 (upstream mechanisms), we acknowledge that H2 and H3 are positioned as exploratory analyses. Findings from these exploratory analyses will inform future adequately powered mechanistic studies. Additionally, while the intervention addresses multiple family stressors, some structural challenges facing refugee populations will lie beyond the intervention’s scope. Finally, we will use caregiver-report of child mental health challenges for the screening, as this is most feasible in real-world settings. While this approach has been validated in other Arabic-speaking populations (Ababneh and Alomari, 2016; Emam et al., 2016), adult proxy-report of the SDQ could result in underreporting of internalising symptoms compared to adolescent self-report. Nonetheless, adolescent-report SDQ will serve as the primary, upstream effectiveness outcome and both adolescent- and caregiver-report SDQ will be measured at all time points. Research assistants are also trained to report observations and disclosures of severe mental health and protection concerns as part of consent, screening and all rounds of data collection, ensuring referral to specialist support for respondents and their families.

